#### Power and sample size calculation

In the previous meta-analysis of maintenance rTMS therapy, the response rates at 3 and 6 months in the group with and without maintenance rTMS therapy were 76.2% and 61.1%, and 56.1% and 38.5%, respectively [29]. Applying the Weibull distribution to the 3- and 6-month response rates, the 12-month response rate was estimated to be 40.9% for the maintenance rTMS group and 20.7% for the no maintenance rTMS group, with an estimated difference of 20%. Considering the relapse and recurrence rates, the previous randomized controlled trial of maintenance therapy in patients who responded to pharmacotherapy reported 44.4% in the pharmacotherapy-only group and 24.2% in the rTMS maintenance therapy group, with a 20.2% difference between the groups [30]. Based on these previous studies, we estimated that the relapse/recurrence rate without maintenance rTMS was 45–60%, and the add-on effect of maintenance rTMS was 20%. To detect a 20% additional effect of maintenance therapy, the required sample size varies from 109 to 130 patients for a 45 ~ 60% relapse/recurrence rate in the pharmacotherapy-only group (chi-squared test with two-sided alpha = 0.05 and power = 80%). Since this study plans to conduct a multivariable analysis adjusting for the background factors, the power was set as high as 90%. Assuming that the proportion of participants who drop out without any evaluation of efficacy is 15%, the required number of participants would be 150 in each group.

From the viewpoint of detection of rare adverse events in the maintenance rTMS group, with 150 participants, at least one event with a 2% probability with a 95% chance is expected. Therefore, based on the perspective of comparing the efficacy and collecting safety information, the target number of study participants was set at 150 in each group, with a total of 300 participants.

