#### Secondary and other outcomes

As for the primary outcome, the rates and between-group differences, and adjusted odds ratio (95% CI) will be estimated for the relapse/relapse rate, response rate, and remission rate at 3, 6, and 9 months after enrollment, respectively. Kaplan–Meier curves will be constructed for the duration of the sustained treatment response and sustained remission, and the log-rank test and Cox proportional hazards models will be performed for the between-group comparisons.

The change in the total scores of the HAMD-17, MADRS, QIDS, and PHQ-9 from the baseline (before the introduction of maintenance therapy) will be analyzed using a random-effects model with group, baseline total score, age, sex, time point, and interaction between the time point and the group as explanatory variables and individual as random effect, for all the data at 3, 6, 9, and 12 months.

Frequency distributions of the worst severity of the adverse events and equipment failure will be summarized. Treatment-related adverse events, serious adverse events, and discontinuations owing to adverse events will also be summarized.

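### The patient random effect in the symptom-score models imposes one variance and one correlation on all four visits, which can misstate standard errors, most reliably for the time-by-group interaction

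*Protocol article*

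**What the plan says.** Under Secondary and other outcomes, the Protocol article analyses "The change in the total scores of the HAMD-17, MADRS, QIDS, and PHQ-9 from the baseline" with one random-effects model per scale. The fixed effects are group, baseline score, age, sex, visit and the visit-by-group product. The visit terms and the within-patient part are given as "time point, and interaction between the time point and the group as explanatory variables and individual as random effect", applied "for all the data at 3, 6, 9, and 12 months". No random slope, visit-specific variance or robust standard error is named.

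The sensitivity analyses (weighting of the primary outcome for treatment choice, and weighting for censoring) do not mention the covariance of the score models. Results are judged two-sided at the 5% level (Statistical analysis).

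On how scores may evolve, the Power and sample size calculation section assumes that "the relapse/recurrence rate without maintenance rTMS was 45–60" per cent, with a rate 20 points lower under maintenance rTMS. Relapse is a HAMD-17 total of 14 or more (Covariates and outcomes). Entry is restricted to patients who responded or remitted after acute rTMS.

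**The concern.** A random intercept with independent, common-variance residuals has two covariance parameters. It forces equal variance at every visit and equal correlation between every pair of visits. This design gives reason to doubt both. Patients enter after a good response, and some then relapse. A growing mixture of well and relapsed patients can widen the spread over the year. Because relapse is a state that lasts for some time, neighbouring visits should also resemble each other more than months 3 and 12 do.

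At stake are the intervals and p-values for the group difference at each visit and for the change in that difference over time, on all four scales.

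**Working it through.** **1. Inputs from the plan.** Relapse by 12 months is 45–60% without and 25–40% with maintenance rTMS. The shapes of the relapse curve come from the plan's own Weibull extrapolation, which reproduces:
- With maintenance: shape = ln[ln 0.611 / ln 0.762] / ln 2 = 0.858, giving a 12-month response of 40.9%, as stated.
- Without maintenance: shape = ln[ln 0.385 / ln 0.561] / ln 2 = 0.724, giving 20.7%, as stated.

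**2. Assumed inputs (none in the documents).** Patient-level SD is 2.5, visit noise SD is 2.5, and the jump at relapse has mean J = 12 (J = 8 as a variant) and SD 3. Relapse is first taken as permanent.

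**3. Formulas (complete data, equal groups).** Let v_t be the variance at visit t and c_st the covariance between visits, both given baseline. Let v̄ and c̄ be their averages over visits and over pairs of visits.
- Model/true standard error at visit t: √(v̄ / v_t).
- Model/true standard error for the month-3-to-12 change in group difference: √[2(v̄ − c̄) / (v_3 + v_12 − 2c_3,12)].
- True type I error at nominal 5%: 2[1 − Φ(1.96 × ratio)].
- With F_t the proportion relapsed by visit t: v_t = F_t(J² + 9) − F_t²J² + 3.125 + 6.25. For s before t: c_st = F_s(J² + 9) − F_sF_tJ² + 3.125. Here 3.125 = 6.25 × 6.25 / 12.5 is the patient variance left after baseline adjustment.

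**4. One case in full: 25% relapse, shape 0.858, J = 12.** F = 0.084, 0.147, 0.201, 0.250, and the variances are about 21.2, 28.7, 34.3 and 38.6 (SD 4.60, 5.36, 5.86, 6.21). So v̄ ≈ 30.7, c̄ ≈ 18.2 and c_3,12 ≈ 12.9.
- Month 3: √(30.7/21.2) = 1.20; type I error 1.8%.
- Month 12: √(30.7/38.6) = 0.89; type I error 8.0%.
- Change from month 3 to 12: √[2 × 12.5 / (21.2 + 38.6 − 25.9)] = 0.86; type I error 9.2%.

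**5. Across 25–60% relapse and both shapes, relapse permanent.**

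| Contrast | Ratio, J = 12 | Type I error, J = 12 | Type I error, J = 8 |
|---|---|---|---|
| Month 3 | 1.07–1.20 | 1.8–3.6% | 2.5–3.6% |
| Month 12 | 0.89–0.98 | 5.5–8.0% | 5.7–7.3% |
| Change, month 3 to 12 | 0.85–0.86 | 9.1–9.5% | 7.6–8.3% |

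A simulation of the J = 12 case (128 per group, 4000 runs, no group difference) gave 1.9–3.9%, 5.4–8.4% and 8.1–8.8%. Month-12-only regression and an unrestricted month-12-minus-month-3 comparison gave 4.7–5.6%.

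A separate mixture with relapse 45% v 25%, shape 0.86 and a 10-point separation gave SDs of 5.28, 5.85, 6.19 and 6.40. With 150 per group the random-intercept standard error is √(2 × 35.3/150) = 0.69 at every visit, against a correct 0.61 at month 3 and 0.74 at month 12.

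**6. If relapsed patients recover.** Let each keep the full jump for three months and half of it afterwards (J = 8 or 12). Month-12 type I error becomes 2.8–5.2%, so the error disappears or reverses. The month-3-to-12 change stays anti-conservative at 5.7–6.9%.

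**7. Variance and correlation separated.**
- SD falling from 6.5 to 5.8: ratios 0.94 at month 3 and 1.06 at month 12, the opposite direction.
- Flat variance, AR(1) correlation ρ between neighbouring visits: single-visit ratios are 1.00 with complete data (0.97–1.03 in simulation). For the month-3-to-12 change the ratio is √[(1 − ρ̄)/(1 − ρ³)] with ρ̄ = (3ρ + 2ρ² + ρ³)/6. At ρ = 0.6: √(0.544/0.784) = 0.83, type I error 10%. At ρ = 0.8: √(0.301/0.488) = 0.79, type I error 12%.

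So the single-visit errors come from unequal variance. The interaction error needs only decaying correlation.

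**The case against.** **The structure is inferred.** The article does not use the term random intercept, and it leaves residual covariance and the standard-error method unstated; these may be in an analysis plan that is not shown. That stands as a caution. Still, the article names a within-patient structure, and an analysis that follows it literally inherits the constraint. The point concerns that stated choice, not missing detail.

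**The direction at single visits is not established.** A reader might infer that month-12 intervals will be too narrow and month-3 intervals too wide. The documents do not support that as fact. They give no SD or correlation by visit. The 25–60% is the proportion ever relapsed, and carrying relapse forward applies to the binary outcome, not to scores. No ceiling on entry HAMD-17 is stated, so a responder who started at 30 could enter at 15. Mixture variance also peaks near 50% relapsed, so at 60% the month-12 error is only about 2–4%. All of this stands.

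**No month-3-to-12 contrast is named as a test.** True, but the visit-by-group product is in the model, and this contrast is one of its components.

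**The stakes are limited.** The primary analysis is a logistic regression, and confounding by preference is a larger threat that the article acknowledges. This stands too.

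**Conclusion.** The point holds in conditional form. As most naturally read, the score models impose equal variance and equal correlation, which this design gives little reason to expect.

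For single visits the error is modest and its direction cannot be known in advance. It is about 2–11% too small at month 12 and 7–20% too large at month 3 if relapse persists, and nil or reversed if patients recover.

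For the time-by-group interaction the error is more dependable. With flat variance, decaying correlation always makes the month-3-to-12 standard error too small, because that pair then has the lowest correlation. With unequal variances it was too small in every relapse scenario in the working. True type I error was about 6–10% there, and 10–12% under flat variance with AR(1) correlation of 0.6–0.8.

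All sizes rest on assumed score distributions. The primary outcome is untouched.

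**What to change.** Keep the fixed effects as listed and replace the patient random effect with an unstructured within-patient covariance over months 3, 6, 9 and 12, estimated by REML, for each of the four scales. If that model does not converge, keep the random effect and report robust (sandwich) standard errors clustered on patient. State this before the data are seen; the trial is listed as ongoing.

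An unstructured 4 × 4 covariance has 10 parameters against 2, so eight more. About 255 evaluable patients (300 × 0.85) support that easily. Kenward–Roger degrees of freedom and a baseline-by-visit term are optional. The latter would change the stated fixed effects and is not needed to cure this problem.

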### Historical control

The primary outcome will also be compared to the 12-month outcomes of the post-marketing surveillance of the NeuroStar TMS system in Japan. The surveillance will include the 300 participants with MDD who received 3 to 6 weeks of acute-phase rTMS therapy in the usual clinical setting and had their prognosis with usual maintenance therapy, which consisted primarily of pharmacotherapy, evaluated.

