## Materials and methods

### Study overview

This study is a multisite, prospective, non-randomized longitudinal trial, recruiting 300 participants, who will be divided into two groups: (I) the maintenance rTMS plus pharmacotherapy group and (II) the pharmacotherapy-only group. The overview of the study is shown in Fig. 1. Only patients who achieve a therapeutic response to acute rTMS therapy will be included in the study. In the maintenance rTMS plus pharmacotherapy group, patients will receive weekly treatments for 6 months, followed by bi-weekly treatments for an additional 6 months, totaling 12 months of maintenance rTMS therapy (maximum 40 sessions). During the maintenance period, the patient will continue with a stable dose of pharmacotherapy. In the pharmacotherapy-only group, patients will receive no intervention other than a continuation of concomitant pharmacotherapy and receive an evaluation. Assessments will be made at 3, 6, 9, and 12 months after the start of maintenance therapy and at the end of study participation. Random allocation to both the groups will not be performed and the patients will be classified to a group (I) or (II) according to their preferences. Owing to the long duration of maintenance therapy immediately following acute treatment in this study, conducting a double-blind, randomized, sham-controlled, parallel-group study was deemed challenging in terms of subject participation and blinding validity.

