### Participants

#### Inclusion criteria

Participants with MDD above the age of 18 years who responded or remitted to 3–6 weeks of acute rTMS therapy will be included. In Japan, rTMS is indicated for patients who have failed to respond to at least one or more antidepressants; thus, these patients will be included in this study. All the participants must understand and be willing to adhere to the 12-month maintenance therapy schedule. The researchers will obtain informed consent from the participants who meet the criteria.

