### RTMS protocol

All the rTMS treatment will be performed using the NeuroStar TMS system (Neuronetics, Inc., Malvern, PA, USA) at a 120% resting motor threshold over the left prefrontal cortex at 10 Hz, with a 4-s stimulation time, 11-s or 26-s inter-stimulation interval, and 3000 pulses/day. The left prefrontal cortex stimulation site was determined by advancing the coil 5.5 cm anterior to the motor threshold location. In the event of problems caused by rTMS therapy stimulation, such as headache, move the coil within 0.5 cm of the stimulation site or rotate it -5 to + 5 degrees around the coil intersection to alleviate symptoms. Participants will be excluded from the intervention if they exhibit unacceptable adverse reactions, are diagnosed with mania or hypomania, or exhibit symptoms that would preclude them from continuing with the trial. Therapists will be in close contact with the participants to increase adherence to the intervention.

Acute-phase rTMS treatment prior to inclusion in this study will be performed as per usual practice in accordance with the Japanese guidelines for the appropriate use of rTMS [32]. Treatment will be administered once daily for up to five days a week, for a maximum duration of six weeks. If patients meet the remission criteria or conversely do not obtain therapeutic effect at the end of three weeks of the treatment, rTMS treatment will be discontinued or gradually tapered off over the course of an additional three weeks. Alternatively, treatment will be continued for 6 weeks. The patients will be administered a stable dose of psychotropic medications during the treatment period.

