### Covariates and outcomes

An overview of the schedule of assessments is shown in Table 1. To ensure the reliability of the assessment, the HAMD-17 and Montgomery–Åsberg Depression Rating Scale (MADRS) will be conducted by clinical or licensed psychologists who have experience in clinical trials. Before the start of the study, we will confirm the agreement of the ratings by using a simulated patient using video clips. In principle, the same evaluator will conduct the evaluation for each participant. In this study, the response is defined as a decrease of 50% or more in the total HAMD-17 score compared to that before the acute phase of rTMS therapy. Remission is defined as a HAMD-17 total score ≤ 7. Relapse/recurrence is defined as a total HAMD-17 score ≥ 14. Cohen's d will be calculated to evaluate the magnitude of the treatment effect for each outcome.

**Table 1 Tab1:** Assessment schedule

	Screening period	Maintenance therapy period				
	1 week	12 months				
	-1 week	0 month	3 month	6 month	9 month	12 month
Screening	◯					
Informed consent	◯					
Patients back ground	◯					
Maintenance rTMS		—△ →	—△ →	—△ →	—△ →	—△ →
Concomitant medications use		★	★	★	★	★
Adverse events		★	★	★	★	★
HAMD-17		◯	◯	◯	◯	◯
MADRS		◯	◯	◯	◯	◯
QIDS		◯	◯	◯	◯	◯
PHQ-9		◯	◯	◯	◯	◯

*HAMD* Hamilton Rating Scale for Depression, *MADRS* Montgomery–Åsberg Depression Rating Scale, *QIDS* Quick Inventory of Depressive Symptomatology, *PHQ-9* Patient Health Questionnaire-9

△: only for maintenance rTMS plus pharmacotherapy group

★: concomitant medication use and adverse events are assessed at each treatment session or outpatient visit

Primary outcome

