Considering feasibility and blinded validity, conducting this study as a double-blind randomized controlled trial is challenging. The total number of sessions in this study is 40 and the duration of maintenance therapy is 12 months, which is considered to be a significant burden for the participants assigned to sham stimulation owing to a large number of sessions and the long duration of the study. Moreover, since all the participants in this study received acute rTMS therapy before entering the maintenance rTMS therapy period, patients may be able to distinguish between real and sham stimulation, which would reduce the blinded validity of the study. Thus, an open-label, nonrandomized study design will be employed in this study.

As mentioned before, the risk of bias owing to the lack of blinding and randomization is a limitation of this study. For example, patients who are favorable to rTMS therapy may be more likely to be assigned to the maintenance rTMS group, resulting in a larger placebo effect and overestimating the effect of maintenance rTMS therapy. We plan to address this point in two ways. The first is to adjust for the background factors by performing IPTW analysis as a sensitivity analysis and attempting to increase the two groups' comparability. However, risk of bias remains because unmeasured confounding cannot be eliminated by an IPTW analysis. Second, the long-term outcome of post-marketing surveillance of the Nerurostar TMS device in Japan will be used as a historical control. Comparing the maintenance therapy group with both the control group in this study and the historical control group may reduce the possibility of overestimating the effect of treatment.

If maintenance rTMS is shown to be effective in preventing relapse/recurrence of depression in this study, the treatment options for patients who have had difficulty maintaining remission with antidepressants and/or psychotherapy will be expanded. Since rTMS is a developing technology, there is no evidence that the current stimulation protocol is the best for treating patients with MDD. The search for optimal protocols for rTMS maintenance therapy and updates to accommodate new rTMS stimulation methods, which are being improved daily, should be continued in future studies.

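### The historical control is described by receipt of acute rTMS, with no stated restriction to responders; if all 300 patients are used, the comparison is expected to favour maintenance rTMS

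*Protocol article*

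**What the plan says.** The Historical control section announces the comparison: "The primary outcome will also be compared to the 12-month outcomes of the post-marketing surveillance of the NeuroStar TMS system in Japan". It then describes the cohort: "The surveillance will include the 300 participants with MDD who received 3 to 6 weeks of acute-phase rTMS therapy in the usual clinical setting", and adds that these patients "had their prognosis with usual maintenance therapy, which consisted primarily of pharmacotherapy, evaluated". The section mentions no condition on response to the acute course.

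The trial population is defined differently. Study overview states: "Only patients who achieve a therapeutic response to acute rTMS therapy will be included in the study". The inclusion criteria agree: "Participants with MDD above the age of 18 years who responded or remitted to 3–6 weeks of acute rTMS therapy will be included".

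Two further places bear on the comparison. Under RTMS protocol, the account of usual acute treatment provides for patients who show no benefit: "If patients meet the remission criteria or conversely do not obtain therapeutic effect at the end of three weeks of the treatment", treatment is stopped or tapered. Under Covariates and outcomes the event is an absolute threshold: "Relapse/recurrence is defined as a total HAMD-17 score ≥ 14".

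The Discussion offers the historical control as one of two answers to the lack of randomization and blinding, the other being IPTW. It says that comparing the maintenance group with both controls "may reduce the possibility of overestimating the effect of treatment". The abstract gives the same purpose for the external data.

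**The concern.** The two populations are selected on different criteria: the trial on responding to acute rTMS, the surveillance cohort, as described, on having received it. A patient without benefit after three weeks has still had three weeks of acute rTMS and so fits the surveillance description, but could not enter the trial.

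The event definition turns this difference into bias. Because relapse is a score of 14 or more, with no stated requirement of prior improvement, a persistent non-responder scores as an event from the outset. That raises the control rate for reasons unrelated to maintenance treatment.

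At stake is the value of the comparison as a safeguard. Group membership follows patient preference, and the Discussion concedes that IPTW cannot remove unmeasured confounding. If the external control leans the same way as the feared preference bias, agreement between the two comparisons could look like confirmation when it is not.

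**Working it through.** The protocol gives no size, power or expected rate for the historical comparison, so there is no figure of its own to reproduce. What can be checked is how far an unrestricted cohort would move the result.

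**Inputs**
- p, relapse rate of responders without maintenance rTMS: 45–60% (Power and sample size calculation).
- Planned effect: 20 points (same section).
- Surveillance size: 300 (Historical control).
- Maintenance group: 150, less 15% dropout, 150 × 0.85 = 127.5, taken as 127.
- r, share of surveillance patients who responded: not in the documents. Assumed 0.4–0.6, with 0.8 as a favourable case.
- q, share of non-responders at HAMD-17 of 14 or more in follow-up: not in the documents. Assumed 0.8, varied below to 0.7 and 1.0.

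**Formula**

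Historical rate if all 300 are used = r·p + (1 − r)·q. The rate wanted is p. The inflation is therefore r·p + (1 − r)·q − p = (1 − r)(q − p). It is positive whenever q exceeds p, and zero when r = 1.

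**Results with q = 0.8**

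| r | p | Historical rate | Inflation (points) |
|---|---|---|---|
| 0.4 | 45% | 0.4 × 0.45 + 0.6 × 0.8 = 66% | 0.6 × 0.35 = 21 |
| 0.5 | 45% | 62.5% | 0.5 × 0.35 = 17.5 |
| 0.6 | 45% | 59% | 0.4 × 0.35 = 14 |
| 0.8 | 45% | 52% | 0.2 × 0.35 = 7 |
| 0.4 | 60% | 72% | 0.6 × 0.20 = 12 |
| 0.5 | 60% | 70% | 0.5 × 0.20 = 10 |
| 0.6 | 60% | 68% | 0.4 × 0.20 = 8 |
| 0.8 | 60% | 64% | 0.2 × 0.20 = 4 |

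**Varying q**

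With r = 0.5 and q from 0.7 to 1.0, the inflation is 12.5–27.5 points at p = 45% and 5–20 points at p = 60%. At the mild end, r = 0.8, q = 0.7 and p = 60% give 0.2 × 0.10 = 2 points.

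**Consequence if a test were run**

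The section specifies no test. As an illustration, take a two-sided 5% comparison of two proportions (normal approximation), 127 against 300, with no true effect, so that the maintenance group relapses at rate p. With q = 0.8 the chance of a significant result in favour of maintenance rTMS is about 0.36 at 8 points of inflation (r = 0.6, p = 60%) and about 0.98 at 21 points (r = 0.4, p = 45%). With r = 0.8 it is about 0.12 (p = 60%) to 0.26 (p = 45%).

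**The case against.** A reader might infer that the historical control will overstate the benefit. The text does not support that certainty. It says whom the surveillance includes, not which of those patients form the comparison set. Relapse is ordinarily counted in people who first improved, and the reference to prognosis under usual maintenance therapy could mean patients who had benefited. This stands as a limit on the claim, but neither reading is stated, and the only selection criterion given is receipt of acute rTMS.

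The net direction also depends on timing. The trial counts relapse cumulatively over visits at 3, 6, 9 and 12 months, whereas the surveillance is credited only with 12-month outcomes. If it assessed patients only then, it would miss interim relapses, which lowers the control rate and works against maintenance rTMS. This stands too. It is a second misalignment rather than a cure for the first, since nothing suggests that the two would cancel.

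The size is largely assumed: r and q appear nowhere in the documents, and p is a planning value. That is correct, and it is why only a range can be given.

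The comparison is also supplementary. The primary analysis is the covariate-adjusted logistic model against the concurrent group, with IPTW and censoring weights as sensitivity analyses, and the Discussion admits residual bias. A reader might infer that the primary result is compromised; it is not.

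Finally, a condensed article may leave adjustment of a supplementary comparison to the full protocol or SAP. So the absence of weighting is not itself the fault here. The population criterion is different, because the article does state one and it does not match the trial's.

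**Conclusion.** The point holds in conditional form. As described, the historical control is selected on receiving acute rTMS and the trial on responding to it. If all 300 patients are used, this mismatch is expected to favour maintenance rTMS by (1 − r)(q − p), provided non-responders score 14 or more oftener than responders relapse. Under the assumed r = 0.4–0.6 and q = 0.8, with p = 45–60%, that is about 8–21 points against a planned effect of 20; at r = 0.8 it is about 4–7.

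These sizes carry no allowance for assessment timing, which could pull the other way. The concurrent comparison, the sample size and the primary conclusion are untouched. What is affected is the claim that this control helps to limit overestimation: used unrestricted, it cannot be relied on for that purpose.

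**What to change.** State that the historical control consists of surveillance patients who met the trial's own response or remission definition at the end of acute rTMS and who did not receive maintenance rTMS. Use the trial's time zero, relapse rule and assessment times. Adjust or weight on the covariates of the primary model where the surveillance recorded them.

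Do not add a requirement of HAMD-17 below 14 to the historical patients alone. The trial has no such entry rule: response is a fall of at least 50%, so a patient going from 30 to 15 qualifies. A one-sided cut would make the control healthier than the trial group. If such a cut is wanted, apply it equally to both.

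If response status at the end of acute treatment was not recorded in the surveillance, do not present this comparison as protection against overestimation.

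The change needs analysis-plan wording and a subset of the surveillance data. The cost is a smaller external sample, for example 0.5 × 300 = 150 patients under an assumed 50% response share, and so lower precision for this supplementary comparison.
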